## Abstract

E7820, a sulphonamide-type anticancer agent, was developed to inhibit angiogenesis by suppressing integrin α2 expression. Although early-phase trials outside Japan established 100 mg/day as the maximum tolerated dose in monotherapy, no objective responses were observed, and further development was not planned. Subsequent studies revealed that E7820 promotes DCAF15-mediated degradation of the splicing factor RBM39 and acts as a molecular glue, providing a novel mechanism and rationale for clinical evaluation. Preclinical screening using patient-derived xenograft models demonstrated antitumour activity in biliary tract and endometrial cancers and in tumours with homologous recombination repair gene alterations. Based on these findings, the CIRCUS trial, a multicentre investigator-initiated phase I study, was initiated to assess the safety, tolerability, and preliminary efficacy of E7820 in Japanese patients with unresectable solid tumours. If the proof of concept is demonstrated in biomarker-defined cohorts, E7820 may be repositioned for selected patients, providing insights into the development of previously intractable compounds.

## Introduction

Advanced or recurrent malignant tumours that cannot be curatively resected are associated with poor prognoses. Epidemiological surveys in Japan have reported that ~980 000 cases of cancer occur annually, of which 18.8% (~350 000 patients per year) have distant metastases [1]. The 5-year relative survival rate for malignancies with distant metastases is reported to be below 20% [1], highlighting the urgent need for further therapeutic development for patients with unresectable advanced or recurrent cancers.

### E7820

E7820 was initially developed by Eisai Co., Ltd., as a sulphonamide-type anticancer agent that inhibits tumour angiogenesis by suppressing the expression of integrin α2 [2].

A phase I trial targeting malignant tumours was conducted overseas (E7820-A001-102 trial, NCT00078637) [3]. In this trial, the starting dose regimen was defined as 10 mg of E7820 administered orally once daily (QD) for 28 days, with a 7-day treatment break included only in Course 1. The tolerability and safety of E7820 were evaluated using a 3 + 3 dose-escalation design at doses of 10, 20, 40, 70, 100, and 200 mg/day. No dose-limiting toxicities (DLTs) were observed in four patients treated with 100 mg/day E7820. However, at 200 mg/day, two of six patients experienced DLTs, including anaemia, neutropenia, thrombocytopenia, abdominal pain, and vaginal bleeding. Subsequently, an additional cohort of 13 patients was administered 100 mg/day E7820. Among the 17 patients treated with this dose, only one DLT was reported.

Based on these results, the maximum tolerated dose (MTD) and recommended phase II dose were determined to be 100 mg QD for 28 days per cycle.

The most frequently observed adverse events (AEs) included Grade 1–2 nausea, fatigue, diarrhoea, and anaemia. Grade 3–4 haematologic toxicities were also observed but were manageable with supportive care. Although 29 of 37 enrolled patients were evaluated for efficacy, no objective responses were observed in the E7820-A001-102 trial. Incidentally, patients with biliary tract or endometrial cancer were not enrolled in this trial.

E7820 is rapidly absorbed following oral administration, achieving mean maximum plasma concentrations (*C*_max_) ranging from 0.19 μg/ml at a dose of 10 mg/day to 1.86 μg/ml at 200 mg/day within 2.17–5.33 h postdose (*t*_max_). Both *C*_max_ and the area under the concentration–time curve (AUC) increased linearly up to a dose of 70 mg/day; however, a nonlinear increase was observed in the dose range of 70–200 mg/day. The mean AUC_0–24_ values ranged from 1.2 μg·h/ml (10 mg/day) to 21.6 μg·h/ml (200 mg/day), and the mean terminal half-life of E7820 was between 5.6 and 8.6 h.

A separate phase I trial (E7820-E044-110 trial [4]) was conducted in patients with unresectable solid tumours to determine the MTD of E7820 administered orally twice daily (BID). This study consisted of two parts: Part A (food-effect study) and Part B (MTD determination for BID dosing). In Part A, the primary objective was to evaluate the effect of a high-fat meal on the oral bioavailability of E7820 (50 mg). Participants were randomized to receive a single 50 mg dose under fasting conditions or immediately after a high-fat breakfast on Day 1, followed by crossover dosing after a 7-day washout period. Although E7820 showed high pharmacokinetic variability (AUC CV: 29%–137%), administration after a high-fat meal caused only a slight delay in absorption (tmax: 4 h vs. 3 h under fasting conditions). The geometric mean ratios (postprandial/fasting) of *C*_max_ and AUC were 1.12 and 1.07, respectively, with 90% confidence intervals including 1, indicating no clinically relevant food effect. Therefore, E7820 can be administered irrespective of food intake. The primary objective of Part B was to determine the MTD of E7820 for BID dosing. MTD was defined as the highest dose at which no more than one of six patients experienced DLT. Two dose levels were evaluated: at 50 mg BID, no DLTs were observed in three patients; at 60 mg BID, two of seven patients experienced DLTs (febrile neutropenia and neutropenia). Consequently, the MTD for BID dosing was determined to be 50 mg. Similar to the previous trial, the best overall response was stable disease, and no objective responses were observed.

Recently, E7820 has been shown to function as a molecular glue that facilitates the interaction between DCAF15—a substrate receptor of the CUL4 E3 ubiquitin ligase complex—and the splicing factor RBM39 (also known as CAPERα) [5–7]. This interaction promotes selective ubiquitination and proteasomal degradation of RBM39. Loss of RBM39 disrupts RNA splicing fidelity and has been implicated in the suppression of cancer cell proliferation, providing a novel rationale for the clinical investigation of E7820 [5–7].

### Background of target population selection

At the National Cancer Center (NCC) in Japan, a patient-derived xenograft (PDX) library, referred to as the J-PDX Library [8], has been established using tumour samples derived from Japanese patients with cancer. As of April 2023, this library comprised ~600 PDX models across various cancer types. Since 2021, NCC and Eisai Co., Ltd., have conducted a research project, supported by the Cyclic Innovation for Clinical Empowerment (CiCLE) programme of the Japan Agency for Medical Research and Development, to evaluate the antitumour efficacy of compounds in Eisai’s development pipeline using rare and refractory cancer models from the J-PDX Library. The CiCLE programme aims to consolidate Japan’s strengths through industry–academia–government collaboration, thereby establishing a fundamentally innovative research foundation. Its objectives include conducting research and development that precisely addresses clinical needs, accelerating the clinical application of pharmaceuticals, medical devices, regenerative medicine products, and related medical technologies and fostering an environment that strongly promotes open innovation and the growth of ventures in the field of medical research and development. As part of this initiative, it was decided to re-evaluate the efficacy of E7820, the mechanism of action of which has been elucidated in recent years.

By April 2023, drug screening for E7820 was performed on 48 PDX models, including 12 pancreatic, 12 biliary tract, 10 gastric, 10 endometrial, 2 lung, 1 ovarian, and 1 breast cancer models.

In these PDX models, efficacy screening was performed by oral administration of E7820 at doses of either 100 or 200 mg/kg for 21 consecutive days. The antitumour effect was assessed by calculating the T/C ratio using the following formula:

\begin{align*} \varDelta \mathrm{T}=\,&\left(\mathrm{Final}\kern0.17em \mathrm{tumour}\kern0.17em \mathrm{volume}\kern0.17em \mathrm{in}\kern0.17em \mathrm{the}\kern0.17em \mathrm{treatment}\kern0.17em \mathrm{group}\right)\nonumber\\&\hbox{--} \left(\mathrm{Initial}\kern0.17em \mathrm{tumour}\kern0.17em \mathrm{volume}\kern0.17em \mathrm{in}\kern0.17em \mathrm{the}\kern0.17em \mathrm{treatment}\kern0.17em \mathrm{group}\right) \end{align*}

\begin{align*} \varDelta \mathrm{C}=\,&\left(\mathrm{Final}\kern0.17em \mathrm{tumour}\kern0.17em \mathrm{volume}\kern0.17em \mathrm{in}\kern0.17em \mathrm{the}\kern0.17em \mathrm{control}\kern0.17em \mathrm{group}\right)\nonumber\\&\hbox{--} \left(\mathrm{Initial}\kern0.17em \mathrm{tumour}\kern0.17em \mathrm{volume}\kern0.17em \mathrm{in}\kern0.17em \mathrm{the}\kern0.17em \mathrm{control}\kern0.17em \mathrm{group}\right) \end{align*}

$$ \mathrm{T}/\mathrm{C}=\left(\varDelta \mathrm{T}/\varDelta \mathrm{C}\right)\times 100 $$

T/C represents the relative change in tumour volume in the treatment group compared with the control group; lower T/C values indicate greater tumour shrinkage.

A previous study [9] presented a waterfall plot of T/C values, illustrating the antitumour efficacy according to cancer type following the administration of E7820 at 100 mg/kg in each PDX model.

Among the PDX models, negative T/C values—indicating tumour shrinkage—were observed in 8 of 12 (67%) biliary tract cancer models and in 6 of 9 (67%) endometrial cancer models, suggesting a strong antitumour effect in these cancer types.

To identify biomarkers associated with E7820-induced tumour shrinkage, whole-exome sequencing was performed on PDX models. Abnormalities in homologous recombination repair (HRR) genes, which are critical for DNA repair pathways, were frequently observed in models that responded to E7820. Notably, tumour shrinkage was detected in models harbouring mutations in *BRCA1*, *BRCA2,* or *ATM*, suggesting that these mutations may serve as potential biomarkers for predicting E7820 efficacy [9].

These results provide a rationale for re-evaluating the safety and efficacy of E7820 in cancers characterized by specific histological subtypes and biomarkers that are predictive of treatment response.

Based on these findings, the CIRCUS trial, a multicentre investigator-initiated phase I study designed to evaluate the safety and tolerability of E7820 in Japan, was initiated.

In addition, this study aims to assess the efficacy of E7820 in patient populations expected to derive clinical benefit, as suggested by the results of efficacy evaluations using PDX models.

## Patients and methods

### Study design of the CIRCUS trial

We designed a multicentre phase I investigator-initiated clinical trial of E7820 in Japanese patients with unresectable solid tumours (the CIRCUS trial; NCCH2303) to evaluate the tolerability and safety of E7820 in this population. The CIRCUS trial will be conducted jointly at the NCC Hospital and NCC Hospital East. The study protocol was approved by the Institutional Review Board of NCC in June 2024 (T5246).

The study comprises two phases: a dose-confirmation phase (Part 1) and an expansion phase (Part 2) (Fig. 1).

**Figure 1 f1:**
[figure not shown]
Schema of the CIRCUS trial.

The dose-confirmation phase (Part 1) is designed to evaluate the tolerability and safety of E7820 in Japanese patients with advanced or recurrent solid tumours that are refractory or intolerant to standard therapeutic regimens, regardless of gene mutation status. In the dose-confirmation phase (Part 1), a 3 + 3 dose-escalation design will be used to determine the recommended dose (RD).

In the expansion phase (Part 2), efficacy and safety data will be collected at the RD determined in Part 1. Based on prior PDX preclinical studies that showed E7820-induced tumour shrinkage in biliary tract and endometrial cancers, irrespective of HRR gene status, as well as in tumours harbouring HRR mutations (*BRCA1*, *BRCA2*, and *ATM*), the following cohorts will be established: Cohort 2–1 (biliary tract cancer), Cohort 2–2 (endometrial cancer), and Cohort 2–3 (solid tumours with HRR gene mutations, such as *BRCA1*, *BRCA2*, or *ATM*).

### Eligibility criteria

#### Inclusion criteria

Table 1 provides an overview of the eligibility criteria. Eligible patients must have histologically or cytologically confirmed solid tumours that are unresectable, advanced, or recurrent. These tumours must be those for which no standard therapy is available or for which standard treatments have proven ineffective or intolerable. Patients must also have an Eastern Cooperative Oncology Group performance status of 0 or 1 and adequate organ function.

**Table 1 TB1:** Eligibility criteria.

**a) Inclusion criteria**	
Histologically or cytologically confirmed malignant solid tumour	
Unresectable, advanced, or recurrent solid tumour	
No standard treatment available or standard therapy has proven ineffective or intolerable	
Eastern Cooperative Oncology Group performance status of 0 or 1	
Expected survival of at least 3 months from the time of enrolment	
At least 18 years of age	
At least one measurable lesion identified on contrast-enhanced computed tomography or magnetic resonance imaging	
Patients must not have previously received treatment with E7820.	
Clinical laboratory tests performed within 14 days before enrolment must demonstrate adequate organ function Neutrophil count ≥1500/mm^3^ Haemoglobin ≥9.0 g/dl Platelet count ≥10 × 10^4^/mm^3^ Creatinine ≤1.5 mg/dl Total bilirubin ≤1.5 mg/dl Aspartate aminotransferase ≤75 (150) U/L (if liver metastases are present) Alanine aminotransferase ≤105 (210) U/L in males and ≤ 57.5 (115) U/L in females (if liver metastases are present)	
SpO_2_ ≥ 92% on room air	
Females of childbearing potential must agree to use effective contraception from the time of providing informed consent until 30 days after the final dose of the study drug and must also agree to refrain from breastfeeding during this period. Male patients are required to use contraception for the same duration.	
All patients must be capable of providing written informed consent and of complying with all study requirements.	
**Cohort 2–1: Biliary tract cancer** Unresectable, advanced, or recurrent biliary tract cancer, which includes intrahepatic cholangiocarcinoma, hilar cholangiocarcinoma, distal cholangiocarcinoma, ampullary carcinoma, or gallbladder cancer	
**Cohort 2–2: Endometrial cancer** Unresectable, advanced, or recurrent endometrial cancer	
**Cohort 2–3: Solid tumour with homologous recombination repair gene mutations** Solid tumour with *BRCA1*, *BRCA2*, or *ATM* gene mutation	

**b) Exclusion criteria**	
Hypersensitivity to sulphonamide derivatives	Patients with a history of unstable ischemic disease, including ischaemic heart disease, myocardial infarction, or other unstable cardiac conditions, within 3 months prior to enrollment
Anticancer treatments, including chemotherapy, molecularly targeted therapy, or immunotherapy within 4 weeks before enrolment	Require anticoagulation or antiplatelet therapy
Any other investigational or unapproved drugs within 4 weeks before enrolment	Active haemoptysis or gastrointestinal bleeding within 3 weeks before enrolment
Underwent major trauma or significant surgical procedures within 4 weeks before enrolment	Active multiple primary cancers, except for cancers that have been completely resected, gastrointestinal mucosal carcinomas that have been curatively treated, or other malignancies with no recurrence for >5 years
Patients who have not recovered to grade 1 or higher from adverse events related to prior treatments, excluding peripheral neuropathy, alopecia, and endocrine disorders controlled with hormone replacement therapy	Left ventricular ejection fraction <50% on echocardiography
Systemic steroid-based immunosuppressive therapy equivalent to ≥10 mg/day of prednisolone within 2 weeks before enrolment	Clinically significant electrocardiogram abnormalities, including QT prolongation with a QTc (Fridericia’s correction) >480 ms
Pregnant, potentially pregnant, or lactating women	Interstitial lung disease or pulmonary fibrosis
Symptomatic brain metastases, carcinomatous meningitis, or progressive central nervous system disorders	Psychiatric disorders or symptoms that interfere with daily functioning or study participation
Spinal metastases requiring radiotherapy or surgical intervention	Antipsychotic drug use or suicide attempts within the past 2 years
Clinically significant pericardial, pleural, or ascitic effusions requiring treatment	Drug or alcohol dependence or abuse within the past 2 years
Patients who had a positive test result for human immunodeficiency virus, hepatitis B virus, or hepatitis C virus	Pulmonary dysfunction requiring active treatment
Active infections requiring systemic treatment	Investigator deems medically or otherwise unfit to participate in the study

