#### Definition of dose-limiting toxicity

A DLT is defined as an AE related to E7820 that occurs during Course 1 (28 days). The details of the DLT definitions are presented in Table 2. AEs will be graded based on the Common Terminology Criteria for Adverse Events (CTCAE) version 5.0 [10], Japan Clinical Oncology Group (JCOG) version [11].

**Table 2 TB2:** Definition of dose-limiting toxicity.

**Haematologic toxicity**	1. Grade 4 neutropenia for ≥8 days Grade 4 neutropenia requiring treatment with granulocyte colony-stimulating factor
	2. Febrile neutropenia
	3. Grade 3 thrombocytopenia for **≥**8 days Grade 3 thrombocytopenia accompanied by bleeding Grade 3 thrombocytopenia requiring platelet transfusion Grade 4 thrombocytopenia
	4. Grade 3 anaemia requiring red blood cell transfusion Grade 4 anaemia
	Grade 4 adverse events
**Nonhaematologic toxicity**	1. Clinically significant grade 3 adverse events (excluding diarrhoea, nausea, and vomiting that resolve to grade 1 or lower ≤7 days with appropriate treatment)
	2. Clinically significant grade 3 or higher laboratory abnormalities

In addition, if an adverse event related to E7820 results in a total administered dose during course 1 that is <75% of the planned dose, it will be considered a dose-limiting toxicity (DLT).

If treatment is discontinued owing to an adverse event not related to E7820 or if <75% of the planned dose is administered in the absence of a DLT, the case will not be subject to DLT evaluation. In such cases, the Trial Steering Committee or Trial Coordination Office will review the situation and consider enrolling a replacement participant.

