#### Endpoints and outcome measures

The primary endpoint is the incidence of DLT.

The clinical hypothesis for the dose-confirmation phase of this study is that the RD of E7820 for Japanese patients is 100 mg/day, administered orally for 28 consecutive days. Because there are no existing data on the administration of E7820 in Japanese patients, tolerability will be evaluated at two dose levels: 70 mg/day (Cohort 1–1) and 100 mg/day (Cohort 1–2). A minimum of 3 and a maximum of 12 participants will be enrolled in the dose-confirmation phase.

Tolerability will be assessed based on the incidence of DLTs observed during the DLT evaluation period, which is defined as treatment course 1 (28 days of E7820 administration).

The starting dose will be 70 mg/day, and the DLT evaluation will begin with three participants.

Secondary endpoints include PK, pharmacodynamics (PD), ORR, duration of response (DoR), disease control rate (DCR), PFS, OS, and the incidence of AEs.

PK/PD analyses will be performed using the pharmacokinetic analysis set (those with appropriate PK data collection) to evaluate the plasma concentrations and pharmacokinetic parameters of E7820 as well as their correlations with efficacy and safety. PK analyses will be performed using noncompartmental analysis with the Phoenix® NLME software (Certara, St. Louis, MO, USA).

Tumour response will be assessed according to the Response Evaluation Criteria in Solid Tumors v1.1 (JCOG version) [12]. Imaging studies for efficacy assessment (computed tomography or magnetic resonance imaging) will be performed every 8 weeks until Week 24 after the initiation of the protocol treatment and every 12 weeks thereafter.

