The ORR is defined as the proportion of patients whose best overall response is complete response (CR) or partial response (PR), as determined by the investigators. The DoR is defined as the period from the first confirmed CR or PR until disease progression or death and will be evaluated in the full analysis set (FAS: patients who received at least one dose, excluding those with evident protocol violations). The DCR is the proportion of patients in the FAS with the best overall response of CR, PR, or stable disease. PFS is defined as the time from enrolment to disease progression or death from any cause, whereas OS is defined as the time from enrolment to death from any cause. AE incidence is defined as the proportion of patients in the safety analysis set (SAS: those who received at least one dose) experiencing each event, with grading based on the worst severity per CTCAE v5.0-JCOG.

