### Statistics

#### Analysis method

Primary analysis will be performed after completing the DLT assessment in the dose-confirmation phase, and the RD of E7820 will be determined. A standard 3 + 3 design will be used. Escalation from Cohort 1–1 to Cohort 1–2 will occur if DLTs are zero in three patients or one or fewer in six patients; otherwise, the continuation of the trial will be reviewed. In Cohort 1–2, if DLTs are one or fewer in six, 100 mg will be confirmed as the RD, and the expansion phase will proceed. The Trial Steering Committee will evaluate the validity of the DLTs at each milestone.

Safety analysis will focus on the frequency and proportion of DLTs. The 95% CI will be calculated using the Clopper–Pearson method. For efficacy, the ORR will be assessed using a binomial test (H0: ORR ≤ 5%) with one-sided 5% significance level. The CIs (90% and 95%) will be calculated for each cohort. Subgroup and supplementary analyses will be performed based on tumour type, genetic alterations, and prior treatments using FAS, SAS, and all enrolled populations.

PFS and OS will be analysed using Kaplan–Meier estimates, with Greenwood’s formula and the Brookmeyer–Crowley method applied to CIs. Additional analyses will include waterfall, spider, and swimmer plots; compliance (dose intensity) summaries; DoR; and time-to-response using both descriptive statistics and Kaplan–Meier estimates.

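### The prior-toxicity exclusion in Table 1(b) is worded with its threshold reversed, so read literally it does not exclude patients with persisting higher-grade toxicity

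*Protocol article*

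**What the plan says.** Table 1(b), the exclusion list, removes "Patients who have not recovered to grade 1 or higher from adverse events related to prior treatments". The same entry then carves three kinds of residual event out of the rule, in the words "excluding peripheral neuropathy, alopecia, and endocrine disorders controlled with hormone replacement therapy". The prose paragraph on exclusion criteria below the table mentions bleeding disorders, anticoagulants, immunosuppressants and interstitial lung disease. It does not repeat or clarify the residual-toxicity criterion.

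Adverse events are graded by CTCAE version 5.0 (JCOG version), and the endpoints section reports incidence "with grading based on the worst severity per CTCAE v5.0-JCOG", so a higher grade means a more severe event.

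Where the article describes resolution of an event elsewhere, in the DLT definition (Table 2), the direction is the opposite. Certain grade 3 gastrointestinal events are set aside if they "resolve to grade 1 or lower ≤7 days with appropriate treatment".

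**The concern.** An exclusion for incomplete recovery should keep out patients whose toxicity from earlier treatment is still too severe. The published sentence sets its bound from below instead of from above. Anyone applying it word for word would find that persisting moderate or severe toxicity does not trigger it.

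Participant safety is the first thing at stake. The trial enrols patients for whom standard therapy has failed or was not tolerated, so leftover toxicity at screening is foreseeable. A stated limit on it is part of what protects them.

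A second, smaller matter is attribution. "The primary endpoint is the incidence of DLT", and it is counted in cohorts of three to six. Carried-over toxicity that worsens in Course 1 could be judged related to E7820 and counted, either directly or through the rule on receiving less than 75% of the planned dose. If it is judged unrelated and treatment stops, the patient leaves the DLT evaluation and a replacement is considered.

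**Working it through.** The point is one of wording. The plan states no figure that depends on it, so there is none to reproduce. The check sets the texts side by side.

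**Step 1: literal reading.** Inputs are the Table 1(b) criterion and the CTCAE scale. The middle column applies the criterion as published. The right-hand column applies the same sentence with the direction used in Table 2. It compares wordings and does not recommend a threshold.

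| Residual grade at screening | Excluded, Table 1(b) as published | Excluded, if the direction of Table 2 were used |
|---|---|---|
| 0 | yes (not at or above 1) | no |
| 1 | no | no |
| 2, 3 or 4 | no (already at or above 1) | yes |

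The two wordings disagree at every grade except grade 1.

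**Step 2: the criterion's own exceptions.** Neuropathy, alopecia and hormone-controlled endocrine disorders are exempted. An exemption does something only if patients with such residual conditions would otherwise be excluded. On the published wording, a patient with any residual neuropathy is at grade 1 or above and is never caught, so the exemption has no effect. The exceptions make sense only if the criterion was meant to limit residual severity.

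**Step 3: other text that might repair it.** The prose on exclusions is silent. Other entry criteria cover parts of the gap:
- neutrophil, haemoglobin, platelet, creatinine, bilirubin, AST and ALT limits within 14 days of enrolment;
- oxygen saturation and performance status;
- ejection fraction and QTc limits;
- exclusions for interstitial lung disease, active infection and recent bleeding;
- the four-week interval since earlier anticancer treatment;
- the investigator's general discretion.

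None of these is a general limit on residual toxicity. The uncovered part is mainly non-laboratory toxicity, for example gastrointestinal or skin events.

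**Step 4: sensitivity of the 3 + 3 rule, as illustration only.** The rule reads "Escalation from Cohort 1–1 to Cohort 1–2 will occur if DLTs are zero in three patients or one or fewer in six patients". For a per-patient DLT probability p, the chance that a dose level passes is

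P(pass) = (1 − p)³ + 3p(1 − p)² × (1 − p)³.

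Suppose, as an assumption, that carried-over events wrongly counted as DLTs add an independent per-patient risk f. Then p is replaced by 1 − (1 − p)(1 − f). For p = 0.10 and f = 0.05 this is 1 − 0.90 × 0.95 = 0.145.

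| True DLT probability | f = 0 | f = 0.05 | f = 0.10 | f = 0.15 |
|---|---|---|---|---|
| 0.05 | 0.973 | 0.910 | 0.824 | 0.725 |
| 0.10 | 0.906 | 0.824 | 0.730 | 0.632 |
| 0.20 | 0.709 | 0.622 | 0.536 | 0.454 |

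The documents give no value for f, and the calculation allows for no correction by committee review. It shows that a 3 + 3 rule is sensitive to miscounted events from any source. It does not measure the effect of this wording.

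**The case against.** The strongest reply has four parts.

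- **Table 1 is a summary.** The article presents it as an overview of the criteria. The ethics-approved protocol and the screening form are not shown and may be worded correctly. This stands. A reader might infer that the trial is in fact enrolling patients with unresolved severe toxicity. The documents do not support that, since they show only that the published criterion is misworded.
- **The intent can be recovered.** Recovery implies improvement, so a patient unchanged at grade 3 has arguably not recovered to anything and remains excluded. No site would exclude only patients at grade 0. This softens the literal reading and lowers the practical risk, but it leaves partial improvement, such as from grade 4 to grade 2, on the wrong side of the published line. A stated threshold should not depend on readers correcting it.
- **The DLT count is protected elsewhere.** A reader might infer that the wording threatens the dose decision. The documents do not support a claim of that strength. A DLT must be related to E7820, the Trial Steering Committee reviews the validity of DLTs at each milestone, and many residual toxicities are screened out by other criteria. It is also true that one extra event turns 0/3 into 1/3 or 1/6 into 2/6, but that holds for any misattributed event in any 3 + 3 trial and is not a measure of this defect.
- **Table 2 is not an entry rule.** Its phrase "that resolve to grade 1 or lower" governs on-study diarrhoea, nausea and vomiting. This stands too. Table 2 shows the article's own direction for resolution, but it is not a competing eligibility criterion.

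**Conclusion.** The criterion is wrong as written. That conclusion needs only the CTCAE ordering and the sentence itself, and the listed exceptions confirm it.

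Its importance lies mainly in participant safety and correct eligibility, for non-laboratory toxicity that the remaining entry criteria miss. An effect on DLT attribution is plausible but secondary. It has not been demonstrated, cannot be sized from the documents, and is limited by the relatedness requirement and the committee review.

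No planned sample size, power or significance level is affected. Whether the error reaches practice depends on the approved protocol and the screening form, neither of which is available here.

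**What to change.** Reconcile the direction of the threshold in Table 1(b) with the approved protocol and with the grade wording in Table 2, and correct whichever text is in error. Which grade should apply is for the approved protocol to settle. Then confirm that the eligibility checklist in use carries the reconciled wording. The article reports that enrolment began in September 2024 and is continuing, so the check is worth making promptly.

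The cost is about a one-word correction in the table and a check of the screening form. No analysis or design element needs to change.
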